### 168 **Allocation concealment**

169 The enrolled patients are allocated to the treatment arm using an electronic randomization system.  
170 This is a secure web-based randomisation system which could be accessed from a desktop  
171 computer.

172 Patient enrollment and allocation to treatment are the responsibility of neonatologists involved in  
173 the study at participating centers.

174 If a baby allocated to PCI procedure will not undergo it, investigators will highlight the timing and  
175 reason for an early cord clamping.

### 176 **Blinding**

177 The study is not blinded and the staff performing the study also care for the infants. However, the  
178 cardiac and cerebral echographic assessments are made by clinicians other than investigators  
179 involved in patient care, and researchers assessing study endpoints are blinded to the study  
180 treatments.

181

### 182 **Study Procedures**

183 Patients are randomly allocated to one of the following treatment groups:

184 – Group I: patients are assisted with the PCI while lying supine on a portable resuscitation trolley  
185 (Lifestart trolley™, Inspiration Healthcare, UK) and the cord is clamped at the end of the 3rd min  
186 of life. In case the treatment is not performed due to maternal or neonatal reasons the infant will  
187 receive an immediate cord clamping.

188 – Group II: patients receive cord UCM without placental refill (milking four times 20 cm of cord at  
189 a speed of about 10 cm/sec) and then clamped before 20 sec of life. In case the treatment is not

190 performed due to maternal or neonatal reasons the infant will receive an immediate cord  
191 clamping.

192 Compliance will be defined as full adherence to the protocol. Compliance with the protocol will be  
193 ensured by a number of procedures included in the site set-up. The local principal investigator  
194 participated in preparatory meetings in which details of the study protocol and data collection were  
195 accurately discussed. All centers received detailed instruction on study procedures and web-based  
196 recording data.

197 All infants will be resuscitated following the current guidelines of the American Academy of  
198 Pediatrics (AAP) (15). Neonatal care will be started with  $\text{FiO}_2$  of 0.30 in both the groups, in  
199 agreement with local protocols. Respiratory support in the delivery room will be given using a T-  
200 piece ventilator (Neopuff Infant T-Piece Resuscitator, Fisher & Paykel, Auckland, New Zealand),  
201 which is a pressure-limited mechanical device that supplies consistent peak inspiratory pressure  
202 (PIP) and positive end expiratory pressure (PEEP), and can deliver sustained inflation (16). Initial  
203 PIP and PEEP values will be set at 20 and 5  $\text{cmH}_2\text{O}$  respectively. To avoid pressure leakage, a  
204 neonatal mask of appropriate size, which adequately covers both the mouth and nostrils of  
205 infants, will be used. The flow rate will be set at 10 L/min without changes during the  
206 resuscitation. Spontaneously breathing babies with a respiratory effort present or with a  
207 suboptimal  $\text{SpO}_2$  on pulse oximeter will be assisted in nCPAP. In the delivery room, infants will be  
208 started on mechanical ventilation (MV) if they have not reached the goal of 70%  $\text{SpO}_2$  by 5  
209 minutes (17) and 85% by 10 minutes of life (18) with a heart rate  $>100$  bpm, despite nasal CPAP  
210 at 5-8  $\text{cmH}_2\text{O}$ .

211 A pulse oximeter (Radical-7, Masimo Corporation, USA) is positioned on Lifestart trolley, and the  
212 trolley, together with all devices placed on it, is covered with a transparent sterile coverage in case  
213 of cesarean section. Thus, the obstetrician hands place the newborn on a completely sterile trolley  
214 and then come back to the mother abdomen, at that moment the neonatologist begin to assist the  
215 baby (with aspiration if necessary, positioning pulse oximeter probe, starting nCPAP/PPV as  
216 necessary). Heart rate will be assessed by auscultation and pulse oximeter. For babies assisted  
217 with an intact cord on Lifestart trolley two person provide bedside neonatal assistance (1 doctor  
218 and 1 nurse). During the 3-minutes period of delayed cord clamping the prevalent procedure will be  
219 to assist respiratory function with nCPAP/PPV till intubation if necessary. If necessary, an early  
220 surfactant administration will be performed in delivery room, but not during the 3-minutes period of  
221 delayed cord clamping.

222 Daily clinical care of the enrolled patients will be performed by the attending physicians in  
223 accordance with the common practice at each center. Daily fluid intake will be started at 80-90  
224 ml/kg and gradually increased by 10–20 ml/kg/day based on changes in body weight, serum  
225 sodium concentrations, and osmolality, with a target intake of 150–160 ml/kg at the end of the  
226 first week of life. In case of hypotension refractory to the fluid-replacement therapy, dopamine

227 and/or dobutamine treatment will be provided. For the treatment of respiratory distress syndrome  
228 (RDS), infants will receive oxygen therapy, respiratory support, and rescue surfactant treatment  
229 to achieve the following therapeutic targets: PaO2 50–60 mmHg, PaCO2 < 65 mmHg, pH > 7.20,  
230 and SpO2 90–95 %. To maintain an adequate SpO2, infants with an FiO2 ≥0.30 will be treated  
231 with surfactant (200 mg/kg Curosurf, Chiesi Pharmaceuticals, Parma, Italy) through the  
232 intubation-surfactant-extubation (INSURE) procedure or less invasive surfactant administration  
233 (LISA) strategy. All infants who will need MV will be treated with surfactant and will then be  
234 gradually weaned from it. Additional doses of surfactant (100 mg/kg) will be given to infants, also  
235 through the INSURE strategy, at the discretion of the attending neonatologist. Infants will be  
236 started on MV when the pH is <7.20 with PaCO2 >65 mmHg, PaO2 <50 mmHg with FiO2 ≥0.50  
237 after surfactant treatment, or if infants have frequent episodes of apnea (>4 episodes in 1 hour or  
238 >2 episodes requiring bag-and-mask ventilation), despite adequate nasal CPAP (5-8 cmH2O)  
239 delivery and oxygenation. MV will be set to maintain a PaCO2 of 55-65 mmHg and SpO2 of 88-  
240 95%. Infants will be extubated when they meet all of the following criteria: FiO2<0.40, PaCO2<65  
241 mmHg with a pH >7.20, MAP ≤7 cmH2O with hemodynamic stability.  
242 Prophylactic antibiotics will be administered from the time of admission to the NICU and will be  
243 stopped after 3 days if the results of the bacterial cultures remain negative.  
244 All newborns will receive continuous cerebral oxygenation monitoring by near infrared  
245 spectroscopy (NIRS), and echographic assessments of cardiac function, and cerebral and  
246 mesenteric blood flow parameters in the first 24 hours of life.

247

## 248 **Participant timeline**

249 The patients enrolled in the trial do not receive extra laboratory tests. A heart ultrasound is  
250 performed in the first 24 hours of life and then repeated until PDA closure or as needed. The  
251 direction of ductal shunt, right and left ventricular stroke volume, and superior vena cava flow are  
252 recorded at the first heart ultrasound. All echographic studies are performed in participating centers  
253 by pediatric cardiologists or by neonatologists trained and certified for neonatal echocardiography,  
254 fulfilling the current recommendations for echocardiography training in the NICU (19).  
255 Serial cerebral ultrasounds for evidence of possible IVH and/or PVL are performed in the first 24  
256 hours of life, at 2, 3, 6, 7 (±1), 15 (±2), and 30 (±2) days of life, and at 40 weeks post-conception.  
257 We will collect severe IVH but also Grade 1 and 2 IVH. We will consider only local reads.  
258 Cerebral oxygenation monitoring by near infrared spectroscopy is performed as soon as possible  
259 after the admission of the newborn in NICU and last 24 hours.

260

## 261 **PROCEDURES**

### 262 **Recruitment and Consent**

263 Women at risk of very preterm birth will be offered participation, and if they accept will give written  
264 consent. Investigators strictly monitor everyday admissions in obstetrics ward and give early  
265 consent to every eligible woman in order to minimize the risk of missing enrolment due to quickly  
266 delivery. Before patients are entered into the study, the parents (or legal representatives) will be  
267 fully informed about the purposes of the study, possible benefits, any potential reasonable risk or  
268 discomfort, the expected duration of the newborn's participation, the clinical and/or functional  
269 procedures, as well as the name of the investigator(s) responsible for conducting the trial and  
270 his/her direct contact details. Written and oral information will be offered to parents, and sufficient  
271 time will be allowed for consent. The newborn will enter the study only after both parents or legal  
272 representatives sign the informed consent form. Eligibility and consent will be checked before  
273 randomization, which will be during labour or before caesarean section.  
274 Whenever antenatal consent is obtained, but the mother passes the term of 30 weeks of  
275 gestation, the infant will not be included in this study.  
276 Non-Italian speaking parents will only be asked for their consent if an adult interpreter is  
277 available. Trust interpreter and link worker services will be used to support involvement of  
278 participants whose first language is not Italian. A senior investigator will be always available to  
279 discuss concerns raised by parents or clinicians during the trial.  
280 A monthly accrual report about the study is sent to participating centers.

281

## 282 **Data Safety and Monitoring Board**

283 Safety and tolerability will be assessed by monitoring the frequency and severity of adverse  
284 events. Safety end-points will include incidence, severity and causality of reported serious  
285 adverse events (SAEs), namely changes in occurrence of the expected common prematurity  
286 complications and routine clinical laboratory test assessments, and the development of  
287 unexpected SAEs in this high risk population. All SAEs will be followed until satisfactory  
288 resolution or until the investigator responsible for the care of the participant deems the event to  
289 be chronic or the patient to be stable. All expected and unexpected SAEs will be reviewed by the  
290 local principal investigators to determine if there is a reasonable suspected causal relationship  
291 with the intervention. A monitoring board including an independent assessor (not involved in the  
292 study) from the IRCCS San Martino Hospital (Genova, Italy) and assessors from each  
293 participating hospital will review all the deaths and adverse effects. If there is a reasonable  
294 suspected causal relationship with the intervention, SAEs will be reported to the Ethics  
295 Committee to guarantee the safety of the participants.  
296 An interim analysis will be performed on the primary endpoint and SAEs from the first 100 infants  
297 enrolled. The interim analysis will be performed by the statistician, blinded for the treatment  
298 allocation, who will report to the principal investigator. The principal investigator will discuss the  
299 results of the interim analysis with the monitoring board and the trial will be ended in case of

300 harm. Criteria for stopping for harm include: 1) a statistically significant difference in SAEs  
301 between the treatment groups, and 2) a reasonable suspected causal relationship between the  
302 intervention and SAEs, and 3) a significant increase in occurrence of SAEs in respect to the  
303 incidence reported in newborns of same gestational age in Vermont Oxford Database.

304

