72 able to rapidly (usually within 20 sec of life) deliver a PT at birth. However, little is known about  
73 the acute physiological effects of UCM and how it influences the cardiovascular transition after  
74 birth. UCM could potentially determine harmful hemodynamic changes similar to those occurring  
75 after immediate cord clamping at birth. To date, all published studies demonstrate that UCM may  
76 have some advantages over immediate cord clamping at birth, such as lower risk for oxygen  
77 requirement at 36 weeks and IVH of all grades, and over short delayed cord clamping, such as  
78 higher initial Hb, higher blood pressure, and improved systemic blood flow and urine output for  
79 infants delivered by cesarean section (7-8).

80 The present study has been designed to assess the effectiveness of assistance with PCI  
81 clamping cord at 3 min of life in comparison with UCM for improving outcome in preterm infants.  
82

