### 92 **Study population**

93 The study is carried out in eight Italian NICUs. The participating centers are listed below:

- 94 - Neonatal intensive Care Unit, Division of Neonatology, Careggi University Hospital of Florence,  
95 Firenze, Italy
- 96 - Neonatal Intensive Care Unit, Division of Neonatology, Fondazione IRCCS “Ca’ Granda”  
97 University Hospital, Milano, Italy
- 98 - Neonatal Intensive Care Unit, “Maggiore” Children Hospital of Bologna, Bologna, Italy
- 99 - Neonatal Intensive Care Unit, Division of Neonatology, “Infermi” Hospital, Rimini, Italy
- 100 - Neonatal Intensive Care Unit, San Bortolo Hospital, Vicenza, Italy
- 101 - Neonatal Intensive Care Unit, Azienda Ospedaliera of Perugia, Italy
- 102 - Neonatal Intensive Care Unit, Di Venere Hospital, Bari, Italy
- 103 - Neonatal Intensive Care Unit, MBBM Foundation, San Gerardo Hospital, Monza, Italy

104  
105 Infants with a gestational age between 23+0 and 29+6 weeks will be eligible for inclusion. Infants  
106 of twin pregnancies or born after placental and cord abnormalities, major congenital  
107 malformations, hydrops fetalis, and maternal severe compromise at delivery will be excluded.  
108

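### Under the written stop-for-harm rule, a randomised between-arm excess of death or severe IVH is not enough on its own; it must also show suspected causality and exceed an outside database whose rate is not stated

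*Combined protocol and SAP*

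**What the plan says.** The protocol (Data Safety and Monitoring Board) plans one interim analysis of the primary endpoint and SAEs in the first 100 infants. The principal investigator then discusses the "results of the interim analysis with the monitoring board and the trial will be ended in case of" "harm. Criteria for stopping for harm include: 1) a statistically significant difference in SAEs" "between the treatment groups, and 2) a reasonable suspected causal relationship between the" "intervention and SAEs, and 3) a significant increase in occurrence of SAEs in respect to the" "incidence reported in newborns of same gestational age in Vermont Oxford Database". These fragments run on from one another, and the three numbered items are joined by 'and' both times.

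The same section describes the safety endpoints as SAEs: "adverse events (SAEs), namely changes in occurrence of the expected common prematurity" complications, laboratory findings and unexpected SAEs. Local principal investigators review each SAE for a suspected causal link. A board made up of one independent assessor and assessors from the participating hospitals reviews all deaths and adverse effects.

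The protocol gives no database rate, no test for the third criterion, no list of SAE types and no separate safety significance level. It does not say whether one arm or both arms together are compared with the database.

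SAP section 5.1 describes the one planned interim as a feasibility look that involved no efficacy variables, and it carries no harm rule. SAP section 2.4 says that enrolment was completed.

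**The concern.** The randomised comparison is the strongest evidence of harm that the trial produces. Under the written rule it is necessary but not sufficient.

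- **Database criterion.** This sets the concurrent arm beside an outside population matched only on gestational age. The trial excludes twins, placental and cord abnormalities, and infants with major "malformations, hydrops fetalis, and maternal severe compromise at delivery will be excluded" (Study population), and it needs antenatal consent. Its background risk may therefore be lower than the database's, although the documents give no figure to confirm this. If it is lower, one arm can be clearly worse than the other without exceeding the database.
- **Causality criterion.** Many of the relevant events are complications of prematurity, where harm shows as a difference in rates. A single severe IVH in a very preterm infant can rarely be attributed to cord management. If this criterion is judged case by case, it can also hold back a randomised signal.

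Harm is foreseen in the documents, and in the control arm too. The Introduction says that "UCM could potentially determine harmful hemodynamic changes similar to those occurring" after immediate clamping, and it links such fluctuations to rupture of cerebral vessels. At stake is whether the infants randomised after the look (212 − 100 = 112 by the protocol, 200 − 100 = 100 by the SAP's sample size) would be covered by a rule that acts on a between-arm signal.

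**Working it through.** **Inputs.** From the protocol's Sample Size Calculation: severe IVH 8.0%, mortality 14.6%, composite 47% v 28%, 80% power, two-sided 0.05, 5% dropout, 106 per group. From Statistical Analysis: two-sided P<0.05. With 1:1 allocation, the look at 100 infants has about 50 per arm. The database rates below are assumptions, shown as a range.

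**The plan's own figure.** With p̄ = (0.47 + 0.28)/2 = 0.375, the pooled-variance formula is

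n = [1.96·√(2·0.375·0.625) + 0.842·√(0.47·0.53 + 0.28·0.72)]² / 0.19² ≈ 100.7 per arm.

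Dividing by 0.95 gives 106.0. The stated 106 per group reproduces (107 if 100.7 is first rounded up to 101). The harm rule has no numerical figure to reproduce.

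**Can the database criterion block a significant between-arm difference?** Take 3/50 v 11/50 deaths. The pooled rate is 0.14, and z = (0.22 − 0.06)/√(0.14·0.86·2/50) = 0.16/0.0694 = 2.31, so chi-square p = 0.021 (Fisher p = 0.041). Criterion 1 is met. Set the database rate at the protocol's own 14.6%. The exact binomial test gives p = 0.16 for 11/50 and p = 1.0 for the pooled 14/100. Criterion 3 fails, so the literal rule is not met.

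**Can the rule be met at all?** Yes. For 7/50 v 16/50, z = 0.18/√(0.23·0.77·2/50) = 2.14 and chi-square p = 0.032 (Fisher p = 0.056). Against 14.6%, 16/50 gives p = 0.002 and 23/100 gives p = 0.023. By chi-square, criteria 1 and 3 both hold.

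**How often?** The true state is a doubling in one arm. All pairs of counts are enumerated:

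Probability = Σ Bin(a; 50, p)·Bin(b; 50, 2p) over the pairs that meet the criteria.

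Criterion 1 is chi-square z > 1.96 in the harmful direction. Criterion 3 is an exact binomial test (two-sided 0.05) showing an excess over the database rate.

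| Event, true rates | Criterion 1 alone | Assumed database rate | 1 and 3, worse arm | 1 and 3, arms pooled |
|---|---|---|---|---|
| Death, 14.6% v 29.2% | 0.43 (Fisher 0.34) | 10% | 0.43 | 0.40 |
| | | 14.6% (base) | 0.41 | 0.24 |
| | | 20% | 0.28 | 0.03 |
| | | 21.9% (1.5 × base) | 0.16 | 0.01 |
| | | 25% | 0.11 | 0.002 |
| Severe IVH, 8% v 16% | 0.24 (Fisher 0.14) | 5% | 0.24 | 0.21 |
| | | 8% (base) | 0.19 | 0.09 |
| | | 12% (1.5 × base) | 0.12 | 0.01 |
| | | 16% | 0.02 | <0.001 |

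The severe IVH figure at 12% depends on the form of the exact test. It is 0.12 with the two-sided version and 0.07 with a one-sided test at 0.025. The death figure at 21.9% is 0.16 under both. Criterion 2 is a judgement and has no number; adding it can only lower these probabilities.

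**False triggers if criterion 1 alone prompts a board decision.** The same enumeration with equal rates in both arms gives 0.027 per direction for death (14.6%) and 0.024 for severe IVH (8%).

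**The case against.** A reader might infer that the rule demands proof that individual events were caused by the intervention, and that the trial therefore could not be stopped, or almost never could. The documents do not support this.

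- The text asks for reasonable suspicion, not proof. The stopping sentence does not say who judges it or that it is judged event by event. A board could base its suspicion on the between-arm pattern itself.
- The list is introduced by 'include', the board reviews all deaths and adverse effects, and SAEs suspected to be related go to the Ethics Committee. Some discretion remains.
- With the only rates the documents give, the database criterion on the worse arm costs little: 0.43 falls to 0.41 for death and 0.24 to 0.19 for severe IVH. The large losses need a higher database rate, which is assumed, or pooled arms.
- Most of the weak detection comes from having 50 infants per arm. Criterion 1 alone misses more than half of true doublings.
- The composite endpoint is not a named trigger, but death and severe IVH can enter criterion 1 as SAEs.
- Asking for corroboration before ending a trial on unadjusted P<0.05 tests is partly a legitimate preference.
- The SAP says enrolment was completed, so new wording cannot protect infants already randomised.

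All of this stands and limits the point. It does not remove it. The two 'and's are in the text, nothing elsewhere makes a between-arm excess sufficient, and discretion that is not written down is not a rule.

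**Conclusion.** The point holds in a limited form. By the written text, a between-arm excess of death or severe IVH would not by itself meet the harm rule, and the database criterion can override a significant randomised difference, as 3/50 v 11/50 shows. The size of the effect cannot be fixed from the documents. For a true doubling with the worse arm compared, the loss runs from almost nothing (database rate 10% for death, 5% for severe IVH) to more than half (0.43 to 0.16 for death, 0.24 to between 0.07 and 0.12 for severe IVH) at 1.5 times the base rate. Pooling the arms lowers the probabilities further. These figures rest on 50 infants per arm, unadjusted two-sided 0.05 tests, the protocol's base rates in the better arm, and assumed database rates.

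This is a weakness to correct and report on. It does not show that the trial had no means of stopping for harm, so it ranks below a must-fix.

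**What to change.** 1. In the Data Safety and Monitoring Board section, make a between-arm excess in either direction sufficient to trigger a formal board decision. Apply it to events already recorded (death, grade 3-4 IVH, total SAEs) at a nominal threshold set by the sponsor. The trigger leads to a decision, not an automatic stop.
2. Keep the causality judgement and the Vermont Oxford comparison as supporting information for the board rather than required conditions. State the database rate, the test and the arm or arms compared.
3. Reconcile that section (interim on the primary endpoint and SAEs at 100 infants) with SAP section 5.1 (feasibility only, no efficacy variables).
4. Since SAP section 2.4 says that enrolment was completed, report whether the interim at 100 infants took place, what it contained, and whether the three criteria were applied jointly.

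The cost is some wording and one interim table from data already collected. The downside is that the board will sometimes deliberate on a chance difference: about 2-3% per event per direction if the threshold were two-sided 0.05, and more across several events.

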### 305 **Statistical Analysis**

306

307 The primary efficacy analysis will be conducted on an intention-to-treat basis and the per-  
308 protocol approach for a secondary sensibility analysis. Clinical characteristics of infants in PCI  
309 and UCM groups will be described using mean values and standard deviation, median value and  
310 range, or frequencies and percentage.

311 Univariate statistical analysis will be performed using the Wilcoxon rank-sum test for continuous  
312 variables and the chi-square test or Fisher's exact test when appropriate for categorical variables.

313 A two-sided P value <0.05 will be considered statistically significant.

314 Relative effect estimates will be expressed as odds ratio (OR) with Wald 95% confidence limits.

315 With explorative intent we will evaluate the heterogeneity of the results within the two groups of  
316 newborns stratified by the type of delivery.

317 Statistical analysis will be performed with SAS System version 9.4 (SAS Institute Inc.).

318

